**FIGURE 1 F1:**
[figure not shown]
Flowchart of the study design.

**TABLE 1 T1:** Study schedule for data measurements.

Study period											
	Enrollment	Allocation	Post allocation								
Timepoint	Pre1	0 d	T0	T1	T2	T3	T4	T5	POD 1	POD 2	POD 3
Enrollment											
Eligibility screen	X										
Informed consent	X										
Random allocation		X									
Interventions											
Active taVNS				X				X			
Sham taVNS				X				X			
Assessments											
Baseline data	X	X									
EEG			X	X	X	X	X	X			
AIS	X								X	X	X
HUAWEI WATCH GT2	X								X	X	X
QoR-15	X								X		
NRS	X								X		
PSQI	X										
HADS-A	X								X	X	X
HADS-D	X								X	X	X
Adverse events	Record at any time at any time at any time										

Pre1 for preoperative day 1, T0, preoperative baseline (5 min before taVNS); T1, preoperative sustained stimulation period (20–30 min taVNS); T2, post-induction (5 min after intubation); T3, intraoperative maintenance (20 min after incision); T4, peri-extubation (end of surgery); T5, postoperative sustained stimulation (20–30 min post-taVNS). POD 1–POD 3 for postoperative days 1–3; taVNS, transcutaneous auricular vagus nerve stimulation; EEG, electroencephalography; AIS, Athens Insomnia Scale; QoR-15, 15-item Quality of Recovery questionnaire; NRS, numeric rating scale; PSQI, Pittsburgh Sleep Quality Index; HADS-A/HADS-D, Hospital Anxiety and Depression Scale-Anxiety/Depression subscale.

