
### EEG power spectrum processing

2.5

Frontal quantitative EEG parameters will be obtained using the ConView YY-105 anesthesia depth monitoring system, employing bilateral frontal electrodes at a sampling rate of 500 Hz. EEG power spectral density will be estimated using the multitaper method (15 tapers, time-half bandwidth product = 8) with a 4-s window length and 50% overlap (2-s step), implemented in MATLAB’s pmtm function. The bandpass filter (0.5–45 Hz) will be applied as a zero-phase filter using forward-reverse filtering to avoid phase distortion. Artifact-free epochs will be extracted at six predetermined time points: T0 (pre-stimulation baseline): 5 min prior to the first taVNS session; T1 (preoperative sustained stimulation), 20–30 min following the initiation of taVNS; T2 (post-induction), 5 min after tracheal intubation; T3 (intraoperative maintenance), 20 min subsequent to the skin incision; T4 (peri-extubation), at the conclusion of surgery, immediately preceding emergence from anesthesia; and T5 (postoperative sustained stimulation), 20–30 min after the initiation of postoperative taVNS.

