#### Secondary outcomes

2.7.2

Trajectory of Postoperative Sleep Quality (1) Subjective sleep quality: The trajectory of AIS total scores from Preoperative Day 1 (Pre-1) through POD 3. (2) Objective sleep parameters: Wrist actigraphy (HUAWEI WATCH GT2) measured continuously from Pre-1 through POD 3. Metrics include sleep continuity (latency, awakenings, wake after sleep onset, efficiency, and total sleep time) and sleep architecture (duration of light, deep, and REM sleep).Anxiety and Depression The Hospital Anxiety and Depression Scale (HADS) will evaluate anxiety (HADS-A) and depression (HADS-D) at Pre-1, POD 1, POD 2, and POD 3. Each subscale comprises seven items scored 0–3; scores ≥ 8 indicate probable anxiety or depression (23).Postoperative Pain and Recovery Quality Pain intensity will be assessed using the Numeric Rating Scale (NRS, 0–10) at rest and during movement on POD 1 (24). Analgesic consumption and patient-controlled analgesia demands will be recorded. Recovery quality will be evaluated on POD 1 using the 15-item Quality of Recovery (QoR-15) questionnaire (scores 0–150, higher scores indicating better recovery) (25).Quantitative EEG Parameters (1) Absolute power: The integral of the power spectral density (PSD) over respective frequency bands (delta 1–4 Hz, theta 4–8 Hz, alpha 8–12 Hz, beta 12–25 Hz, and gamma 25–45 Hz). (2) Peak frequency: The frequency at which maximum PSD occurs within each band.

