### Statistical analysis

2.11

Statistical analyses will be performed using SPSS Statistics 26.0 (IBM Corp.) and R 4.4.0 (R Foundation). MATLAB R2018b (MathWorks, Natick, MA) will be employed for the preprocessing and spectral analysis of EEG data. Normality will be assessed using the Shapiro-Wilk test and Q-Q plots. Continuous variables will be presented as mean ± standard deviation or median (interquartile range), and categorical variables will be shown as frequencies and percentages.

The primary outcome (incidence of AIS ≥ 6 on POD 1) will be analyzed using the chi-square test to compare proportions between the taVNS and sham groups. The effect size will be expressed as an absolute risk reduction with a 95% confidence interval. Linear mixed-effects models will analyze repeated measures, including (1) AIS total scores (Pre 1 to POD 3); (2) HADS-A and HADS-D (as two separate scales, Pre 1 to POD 3); (3) objective sleep parameters from actigraphy; and (4) EEG spectral power across five bands (delta, theta, alpha, beta, and gamma) at six time points (T0–T5). Models include fixed effects for group, time, group × time interaction, and random intercepts for subjects. For repeated clinical outcomes, Bonferroni correction will be applied across four key endpoints: HADS-A, HADS-D, AIS trajectory, and objective sleep parameters from actigraphy, yielding a significance threshold of α = 0.0125 (0.05/4). For EEG spectral analyses, given the exploratory nature and high dimensionality (5 frequency bands × 6 timepoints), the Benjamini–Hochberg procedure will control the false discovery rate at q < 0.05.

A three-step approach will be used to identify predictors of POSD: (1) Univariate screening (*P* < 0.10) for 30 EEG variables (5 bands × 6 timepoints); (2) LASSO regularization (10-fold CV) to select independent predictors; (3) Multivariable logistic regression reporting ORs and 95% CIs.

The main analysis will adhere to the intention-to-treat methodology. To address missing data, multiple imputation via chained equations will be utilized, generating 20 imputations under the assumption that data are missing at random. Sensitivity analyses will incorporate pattern-mixture models to account for mechanisms where data are missing not at random. The per-protocol analysis will exclude cases with significant protocol deviations. Effect sizes will be reported as Cohen’s d, alongside 95% confidence intervals.

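### A random-intercept-only model with a free baseline difference is likely miscalibrated for EEG across awake and anaesthetised states, and uses the clinical baselines inefficiently

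*Protocol article*

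**What the plan says.** The protocol article, section 2.11, gives a single specification for every repeated outcome: "Models include fixed effects for group, time, group × time interaction, and random intercepts for subjects". It states no residual covariance, time-specific variance, robust standard error or baseline covariate.

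The pre-treatment measurement is among the modelled timepoints. For the clinical scales the range is "AIS total scores (Pre 1 to POD 3", and HADS likewise; section 2.7.2 has actigraphy running from Pre-1. For EEG the outcome is "EEG spectral power across five bands (delta, theta, alpha, beta, and gamma) at six time points (T0–T5", and section 2.5 defines "T0 (pre-stimulation baseline): 5 min prior to the first taVNS session".

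The six EEG timepoints span different brain states. T0 and T1 precede induction. The Table 1 footnote then lists "T2, post-induction (5 min after intubation); T3, intraoperative maintenance (20 min after incision); T4, peri-extubation (end of surgery". T5 falls during the second stimulation session, which starts 5 min after extubation (section 2.6). The quantity defined in section 2.7.2 is "Absolute power: The integral of the power spectral density (PSD) over respective frequency bands", with no transformation mentioned.

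On status, section 2.7.2 lists quantitative EEG under secondary outcomes, while section 2.11 treats it as exploratory with false discovery rate control. The primary outcome is tested by chi-square, outside this model.

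**The concern.** A random intercept with independent, equal-variance residuals is a compound-symmetry model. Every timepoint has the same variance, and every pair of timepoints the same correlation. Propofol-remifentanil anaesthesia changes EEG band power markedly. The Discussion itself says that anaesthetic agents disturb the balance of slow and fast waves. It would be surprising if between-patient spread were the same awake and anaesthetised, or if T0 correlated with T1 no better than with T3.

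If the assumption fails, one pooled residual variance is applied to contrasts whose true variances differ. The timepoints most exposed are T1 and T5, the only EEG recordings taken during stimulation. Benjamini-Hochberg control cannot repair this, because it takes the p-values as valid.

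The second issue is separate. Randomisation makes the expected baseline means equal, yet the model estimates a baseline group difference. A group × time contrast against baseline is then a comparison of change scores, which has a larger variance than a baseline-adjusted comparison.

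**Working it through.** **The plan's own figures.** The protocol gives no SD, correlation or power for the mixed models, so there is no figure of theirs to reproduce on this point. The sample size does reproduce with the unpooled-variance formula: (1.96 + 0.842)² × (0.45×0.55 + 0.20×0.80) / 0.25² = 7.85 × 0.4075 / 0.0625 ≈ 51.2, so 52 per group. Then 52/0.9 ≈ 57.8, so 58 per group and 116 in total. None of this depends on the mixed models.

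**EEG inputs.** From the protocol: n = 52 evaluable per group (section 2.10) and t = 6 timepoints. Assumed: the covariance matrix S, in units of the awake SD, with T0, T1 and T5 as one state and T2-T4 as the other. Data are taken as complete.

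**Formulas**, for the group difference in change from T0:
- pooled residual variance under the stated model: m = (tr S − 1′S1/t)/(t − 1)
- model SE = √(4m/n)
- true SE = √(2·Var(change)/n)
- actual two-sided error at nominal 5% = 2·[1 − Φ(1.96 × model SE/true SE)]

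**Case A: SD doubled at T2-T4, correlation 0.5.** tr S = 15 and 1′S1 = 48, so m = (15 − 8)/5 = 1.4 and the model SE is √(5.6/52) = 0.328.
- T1/T5: Var(change) = 1 + 1 − 1 = 1, true SE = √(2/52) = 0.196, ratio 1.67, error about 0.1%. For a 0.6 SD effect, correct power is Φ(0.6/0.196 − 1.96) = 86%. Under the stated model it is Φ((0.6 − 1.96×0.328)/0.196) = 41%.
- T2-T4: Var(change) = 1 + 4 − 2 = 3, true SE = √(6/52) = 0.340, ratio 0.97, error about 5.8%.

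**Case B: SD 1.5 times, correlation 0.5.** tr S = 9.75 and 1′S1 = 33, so m = (9.75 − 5.5)/5 = 0.85 and the model SE is 0.256. At T1/T5 the ratio is 1.30 and power 69% instead of 86%. At T2-T4 the ratio is 0.99.

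**Case C: equal SDs, correlation 0.7 within state and 0.3 between.** The mean correlation is (6×0.7 + 9×0.3)/15 = 0.46, so m = 0.54 and the model SE is √(2.16/52) = 0.204.
- T1/T5: Var(change) = 0.6, true SE 0.152, ratio 1.34, error 0.9%.
- T2-T4: Var(change) = 1.4, true SE 0.232, ratio 0.88, error 8.5%.
- The simulated error of the group × time omnibus test is 7.9%.

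**Case D: compound symmetry.** All ratios are 1.00 and the omnibus error is 5.0%.

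| Assumed covariance | SE ratio T1/T5 | SE ratio T2-T4 |
|---|---|---|
| A: SD ×2, correlation 0.5 | 1.67 | 0.97 |
| B: SD ×1.5, correlation 0.5 | 1.30 | 0.99 |
| C: equal SD, 0.7/0.3 | 1.34 | 0.88 |
| D: compound symmetry | 1.00 | 1.00 |

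**Check with fitted models** (120 simulated fits, SD ×2 with correlation 0.7/0.3). The stated model reported SE 0.332 at both T1 and T3, while the estimates' empirical SDs were 0.141 and 0.349. Constraining the baseline but keeping the random intercept gave SE 0.280 at both, against 0.153 and 0.342. The baseline constraint alone therefore does not cure the EEG standard errors.

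**Baseline efficiency** (equal SDs σ, correlation ρ with baseline). Change contrast variance: 4σ²(1 − ρ)/n. Baseline-adjusted variance: 2σ²(1 − ρ²)/n. Their ratio is (1 + ρ)/2:

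| ρ | Ratio | Variance saved |
|---|---|---|
| 0.3 | 0.65 | 35% |
| 0.5 | 0.75 | 25% |
| 0.7 | 0.85 | 15% |
| 0.8 | 0.90 | 10% |

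**The case against.** The best defence is that the section says what the models include, not that residuals are independent with equal variance. A random intercept can be combined with time-specific residuals, and an unseen analysis plan may do so, or may set a log scale that removes much of any variance difference. That stands as a reason for conditional wording. It does not remove the point: a specific model is published, and read with software defaults it is compound symmetry.

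A reader might infer that the EEG standard errors are simply wrong. The documents do not support that. They give no EEG covariance, and Case D shows the model can be exact.

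A reader might also infer that baseline data are thrown away. They are not. T0 and Pre-1 are in the model, and the contrast against them is unbiased under randomisation. With equal SDs and correlation above 0.5, it already beats a comparison ignoring baseline. The loss is one of efficiency, and it is small when correlation is high.

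Nor should the halved power of Case A be joined to the inflated error of Case C as one result. They come from different assumed matrices, and in Case A the anaesthetised timepoints are close to nominal.

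For AIS the covariance issue looks small: two assumed AIS-type matrices gave omnibus error of about 5.3%. An AR(1) correlation of 0.6 over four visits does give about 10% for the last-visit contrast, but only 2.2% for the first, so quoting the last visit alone would be selective.

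Finally, the stakes are limited. EEG is labelled exploratory, and only secondary and exploratory results are touched.

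**Conclusion.** The point holds in conditional form. As published, the model is likely miscalibrated for EEG. Under the assumed covariances A to C, change-from-T0 standard errors at the stimulation timepoints are 1.3 to 1.67 times too large. At T2-T4 they range from near nominal to 12% too small. The direction and size depend on SDs and correlations that the protocol does not give, and there is no error under compound symmetry.

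For AIS, HADS and actigraphy the finding is mainly lost precision: about 10% to 35% of the variance of the change contrast for correlations of 0.8 down to 0.3, assuming equal SDs. This matters somewhat more because those outcomes are tested at 0.0125.

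It would be wrong to read this as a threat to the trial's main conclusion. The chi-square test of the primary endpoint and N = 116 do not use these models.

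**What to change.** For each repeated outcome, replace the random intercept with an unstructured residual covariance over timepoints, or at least allow time-specific residual variances and correlations. Either enter baseline as a covariate and model only post-baseline timepoints, or keep baseline as an outcome with a common mean in both arms. Report group contrasts at post-baseline timepoints. For EEG, consider analysing log power. The covariance and the baseline changes are both needed, since the baseline constraint alone leaves the EEG standard errors miscalibrated.

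The cost is t(t + 1)/2 covariance parameters: 10 for four visits and 21 for six EEG timepoints, which is manageable with 116 patients. It also needs slightly more code in R, which the plan already names. No extra data or patients are required. The choice should be fixed before unblinding so that the covariance is not selected from the results.

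### The Bonferroni threshold of 0.0125 counts eight actigraphy metrics as one endpoint, so it does not guarantee 5% family-wise error for the repeated secondary outcomes

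*Protocol article*

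**What the plan says.** Section 2.11 (Statistical analysis) assigns linear mixed models to the repeated measures. For the clinical ones it fixes a multiplicity rule: "Bonferroni correction will be applied across four key endpoints: HADS-A, HADS-D, AIS trajectory, and objective sleep parameters from actigraphy". From this it derives a level of 0.0125 per endpoint, that is, 0.05 divided by four.

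Section 2.7.2 (Secondary outcomes) sets out what the actigraphy item contains: "sleep continuity (latency, awakenings, wake after sleep onset, efficiency, and total sleep time) and sleep architecture (duration of light, deep, and REM sleep"). That is five continuity metrics and three architecture metrics, eight in all.

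The same analysis section takes more care elsewhere. HADS enters as "HADS-A and HADS-D (as two separate scales, Pre 1 to POD 3"), and each subscale has its own place in the count of four. The EEG power analyses are counted as bands by timepoints and get separate false discovery rate control. For actigraphy, the article gives no composite score, no lead metric, no joint test and no further adjustment.

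**The concern.** A Bonferroni divisor has to match the number of tests it covers. The eight watch metrics are measured in different units (minutes, counts, a percentage), so one univariate mixed model cannot serve for all of them. With a separate model for each, the divisor of four is too small for the outcomes listed.

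What is at stake is the credibility of an objective sleep finding. The primary endpoint is a self-reported scale, and the Discussion introduces the watch because subjective scales are open to recall bias. A single watch metric below 0.0125 would be a natural companion to the primary result, and readers would take it as protected by the stated correction. With eight chances at that threshold, the protection is weaker than the 0.05/4 in the text implies.

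**Working it through.** **Inputs**
- Overall level 0.05, four counted endpoints, threshold 0.0125: section 2.11.
- Actigraphy metrics: 5 continuity + 3 architecture = 8: section 2.7.2.
- Other outcomes in the family: AIS trajectory, HADS-A and HADS-D = 3: section 2.11.
- Model terms: "Models include fixed effects for group, time, group × time interaction, and random intercepts for subjects". I assume one group-related test per outcome; testing both the group and the interaction term would add tests.
- Correlations between outcomes: not given, so a range is assumed.

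**Step 1. Reproduce the plan's figure.** 0.05/4 = 0.0125, as stated. With four single tests the bound is 4 × 0.0125 = 5.0%, and under independence 1 − (1 − 0.0125)^4 = 4.9%. The arithmetic is right for four tests.

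**Step 2. Count the tests described.** 3 + 8 = 11.

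**Step 3. Error with 11 tests at 0.0125.**
- Upper bound: 11 × 0.0125 = 13.75%.
- Independent: 1 − (1 − 0.0125)^11 = 12.9%.
- Watch block alone: bound 8 × 0.0125 = 10.0%; independent, 1 − (1 − 0.0125)^8 = 9.6%. Its share under the plan is 1.25%.

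**Step 4. Allow for correlation.** Simulation with 400,000 draws, two-sided z tests at 0.0125, no true effects, and a common correlation r:

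| r | Watch block alone | All 11; r among the eight watch metrics, other three independent | All 11 share r |
|---|---|---|---|
| 0.3 | 8.8% | 12.2% | 11.5% |
| 0.5 | 7.5% | 10.9% | 9.5% |
| 0.7 | 5.8% | 9.2% | 7.0% |
| 0.9 | 3.5% | 7.0% | 3.9% |

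If only the watch metrics correlate, the family error returns to 4.9% only at r = 1, where the eight act as one test. If all 11 share the correlation, it falls below 5% somewhere between r = 0.7 and r = 0.9.

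**Step 5. Check the repairs.**
- One key metric: four tests at 0.0125, bound 5.0%.
- Eleven tests at 0.05/11 = 0.0045 (also Holm's smallest threshold): bound 5.0%; 4.9% if independent.
- Split share: 3 × 0.0125 + 8 × (0.0125/8) = 0.0375 + 0.0125 = 5.0%, with 0.0125/8 = 0.0016 per metric.

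**The case against.** The best reply has three parts.

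First, the article never says that each metric will be tested at 0.0125 or that any one of the eight would count as success. That is correct. A reader might infer that the plan licenses an any-of-eight claim, but the text contains no decision rule for the block and does not call these outcomes confirmatory. The error figures are therefore conditional on per-metric testing. What remains is that 0.0125 is the only threshold offered for a plural item; if another rule was meant, the same sentence needs correcting.

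Second, how the block is handled internally could be left to an analysis plan that is not shown. This would answer mere silence. Here the article has already fixed a divisor and a threshold, and they do not match its own outcome list.

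Third, the metrics overlap by construction: total sleep time with the stage durations, and efficiency with total sleep time and wake after sleep onset. Strong correlation lowers the inflation, and the lower rows of the table show by how much. It does not restore 5% over most of the assumed range.

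A reader might also infer that leaving QoR-15 and NRS out of the family is a fault. The documents do not support this: the correction is limited to repeated clinical outcomes, and these two have one postoperative assessment each, on POD 1. Nor does the Discussion single out sleep efficiency as the lead metric; it mentions efficiency and wake after sleep onset together, as examples.

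**Conclusion.** The point holds for the secondary outcomes. The threshold of 0.0125 is correct for four tests but does not guarantee 5% family-wise error for the 11 outcomes that the article places under it. On the natural reading the error is 12.9% under independence, and roughly 4% to 12% across the assumed correlations of 0.3 to 0.9, mostly above 5%. This rests on separate testing of each watch metric, one group-related test per outcome, and equal correlations that the article does not supply.

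A reader might take this as a threat to the trial's main conclusion. It is not: the primary outcome is a single chi-square comparison of AIS ≥ 6 on POD 1, and its level and sample size do not depend on this rule. The severity is moderate.

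**What to change.** Amend the multiplicity sentence in section 2.11 before unblinding, in one of three ways:

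- Name one actigraphy metric as the key objective endpoint, keep 0.0125 for the four endpoints, and label the other seven metrics descriptive. This is the simplest repair and leaves the stated threshold intact. The choice of metric is the sponsor's.
- Apply Holm across all 11 tests, with a smallest threshold of 0.0045.
- Keep 0.0125 for AIS trajectory, HADS-A and HADS-D, and split the actigraphy share to 0.0016 per metric.

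The same sentence should say which model term is the test for each outcome.

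No extra participants or data are needed. Under the first option seven metrics become descriptive. Under Holm all 11 outcomes face a stricter starting threshold, and under the split only the watch metrics do. Timing matters: a lead metric chosen after the results are known would be open to the charge of selective reporting.

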### Randomization and blinding

2.3

An independent statistician will use SPSS (version 26.0, IBM Corp.) to create the allocation sequence through permuted block randomization with randomly varying block sizes of 4 and 6, ensuring balanced allocation throughout the enrollment periods. Participants will be randomly allocated to either active taVNS or sham stimulation in a 1:1 ratio. The statistician will prepare sequentially numbered, sealed, opaque envelopes with group assignments, which will be stored in a locked cabinet accessible solely to a designated unblinded device coordinator. This coordinator responsible exclusively for device preparation will open the envelopes and configure the devices in the pre-anesthesia holding area. Following device connection, the coordinator will exit and have no further contact with participants, clinical care, or outcome assessments.

Throughout the trial, group allocation will remain concealed from anesthesia providers, surgeons, outcome assessors, postoperative ward staff, participants, and data analysts. To ensure participant blinding, identical electrode placement and device appearance will be used for both groups. All devices will display identical interface indicators regardless of stimulation status. Participants will be informed that “both interventions involve ear stimulation with variable mild sensations; individual perception does not indicate assignment.” To maintain assessor blinding, the unblinded device coordinator will ensure that the device interface remains concealed from clinical staff and will not participate in any outcome assessments. Unblinding will be permitted only for serious adverse events that require knowledge of allocation for clinical management. The principal investigator will hold the master randomization key in a sealed, signed envelope. All unblinding events will be recorded along with their reasons and timestamps.

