### Sample size calculation

2.10

The primary outcome is the incidence of POSD on POD 1, defined as an AIS score ≥ 6. Based on our internal pilot study (*N* = 20; taVNS *n* = 10, sham *n* = 10), the incidence of POSD (AIS ≥ 6) was 20% in the taVNS group compared to 45% in the sham group. Sample size was calculated using PASS 15.0 (NCSS, LLC) for a two-sided chi-square test comparing two independent proportions, with the following parameters: P1 (sham) = 0.45, P2 (taVNS) = 0.20, α = 0.05 (two-sided), power = 0.80. This calculation indicated a need for 52 evaluable participants per group. Accounting for an anticipated 10% dropout rate based on comparable perioperative neuromodulation trials, the final target enrollment is 116 participants (58 per group).

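### Single-step Bonferroni at 0.0125 for the four key repeated endpoints is valid, but Holm's step-down procedure keeps the same 5% family-wise error and never rejects less (optional improvement)

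*Protocol article*

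**What the plan says.** Section 2.11 (Statistical analysis) analyses the repeated clinical outcomes with linear mixed models: "Models include fixed effects for group, time, group × time interaction, and random intercepts for subjects". For multiplicity it states that "Bonferroni correction will be applied across four key endpoints: HADS-A, HADS-D, AIS trajectory, and objective sleep parameters from actigraphy". The level for each endpoint is given in the same sentence: "yielding a significance threshold of α = 0.0125 (0.05/4"). The exploratory EEG analyses are handled separately, with Benjamini-Hochberg.

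The primary endpoint lies outside this family: "The primary outcome (incidence of AIS ≥ 6 on POD 1) will be analyzed using the chi-square test". Section 2.10 sizes the trial on that endpoint alone ("P1 (sham) = 0.45, P2 (taVNS) = 0.20, α = 0.05 (two-sided), power = 0.80") and sets no power target or effect size for the four secondary endpoints. The intervals that section 2.11 mentions are ordinary 95% intervals. It states no Bonferroni-adjusted (98.75%) intervals.

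**The concern.** Single-step Bonferroni holds every p-value to 0.0125, however many of the other hypotheses have already been rejected. Holm's procedure holds only the smallest p-value to 0.0125 and relaxes the threshold after each rejection. Both guarantee a family-wise error of at most 5% without any assumption about dependence. For testing, Bonferroni is therefore dominated: at the same guarantee it can lose rejections and never gains any.

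What is at stake is power for secondary claims. The trial is sized for a binary day-1 endpoint, so nothing in the plan reserves power for these four endpoints at a stricter threshold. The Discussion expects effects on more than one of them: it presents the treatment as multi-target and suggests that less anxiety may in turn help sleep. If that is right, several of the four null hypotheses are false, and that is where the two procedures differ.

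**Working it through.** **1. The plan's figure.** 0.05 / 4 = 0.0125. It reproduces exactly.

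**2. The two rules for four members.** Order the p-values from smallest to largest.
- Bonferroni: reject each p ≤ 0.0125.
- Holm: compare in turn with 0.05/4 = 0.0125, 0.05/3 = 0.0167, 0.05/2 = 0.025 and 0.05/1 = 0.05, and stop at the first failure.

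No Holm threshold is below 0.0125, so every Bonferroni rejection is also a Holm rejection. The first step is the same, so the chance of at least one rejection is identical.

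**3. Power under a stated assumption.** The protocol gives no effect sizes for these endpoints. Assume one test per endpoint and 80% power at two-sided 0.05 for each real effect:
- non-centrality = 1.960 + 0.842 = 2.802
- Bonferroni critical value (two-sided 0.0125) = 2.498
- Bonferroni power = Φ(2.802 − 2.498) = Φ(0.304) ≈ 62%, whatever the correlation

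Holm's power was simulated with 200,000 sets of four correlated z statistics (correlation 0, 0.3, 0.6):

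| Real effects | Bonferroni, average per real endpoint | Holm |
|---|---|---|
| 1 of 4 | 62% | 62% |
| 2 of 4 | 62% | 64-65% |
| 3 of 4 | 62% | 67-68% |
| 4 of 4 | 62% | 71-73% |

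With all four real, the chance of confirming all four is 15-35% under Bonferroni and 38-56% under Holm. Holm's family-wise error was at most 4.9% in every setting.

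**4. Sensitivity to the assumed effect.** A second simulation (400,000 runs) used 52 per arm, the evaluable number in section 2.10, with correlation 0 to 0.7. The standardised effects d are assumed:

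| Scenario | Bonferroni | Holm |
|---|---|---|
| one real, d = 0.5 | 52% | 52% |
| two real, d = 0.5 | 52% | 54% |
| four real, d = 0.3 | 17% | 18-20% |
| four real, d = 0.5 | 52% | 60-62% |
| four real, d = 0.6 | 71% | 79-82% |

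With no real effects, the family-wise error was 3.7-4.9%, identical for the two methods.

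**5. Role of correlation.** With four real effects at non-centrality 2.802, Holm's average power falls from 72.7% to 70.6% as the correlation rises from 0 to 0.6, so the gain shrinks slightly. With weak effects (d = 0.3) it grows slightly: Holm rises from 18% at correlation 0 to 20% at 0.7. Neither shift compares with the effect of moving from one real endpoint to four.

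**The case against.** The strongest reply is that nothing here is wrong. Bonferroni is prespecified, valid under any dependence, correctly computed and consistent with the rest of the document. On this view, choosing between two valid procedures is a matter of taste, and every plan that uses Bonferroni would be open to the same criticism. The family is also secondary, the chance of at least one rejection does not change, and a single threshold is simple and has directly matching simultaneous intervals.

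Much of this stands. There is no error in the plan, and neither the primary test nor type I error control is affected. What does not stand is that the choice is only taste. For testing, one rule is never worse than the other and sometimes better, at the same guarantee. The interval argument is sound in general but is not used here, because the stated intervals are ordinary 95% ones.

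A reader might infer that the fixed threshold will needlessly miss real secondary effects, or that it costs most because the endpoints are correlated. The documents support neither. They give no effect sizes for these endpoints, so no actual loss can be shown. The gain is nil with one real effect and about 2 points with two. Holm makes no use of correlation. The large contrast in the chance of confirming all four endpoints concerns a goal that the protocol does not set.

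**Conclusion.** The point holds as an optional improvement, not as a defect. Section 2.11 uses a valid, correctly computed correction that Holm's procedure dominates for testing. That dominance needs no assumption about effect sizes or dependence.

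The size of the gain does need assumptions. At 80% power per real effect, it is 0, 2-3, 5-6 and 9-11 percentage points of average power with one, two, three and four real effects. It is smaller if the effects are weak: 1-3 points with all four at d = 0.3. The gain matters materially only if three or four of the endpoints truly respond and are reasonably well powered. The conclusion on the primary endpoint and the sample size do not change.

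A separate matter is that section 2.7.2 lists eight actigraphy metrics (five for continuity, three for architecture), while section 2.11 counts actigraphy as one family member. Holm with four members does not settle that.

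**What to change.** Optional, before unblinding: in section 2.11, replace the fixed 0.0125 threshold with a sentence such as: *The four key repeated clinical endpoints will be tested with Holm's step-down procedure at a family-wise two-sided α of 0.05 (ordered thresholds 0.0125, 0.0167, 0.025 and 0.05).* Report Holm-adjusted p-values beside the 95% intervals already planned. If the family count changes once the actigraphy member is defined, the same rule applies with the new number of members.

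The cost is one sentence, with no extra participants, visits or data and no loss of error control. The downside is that Holm has no simple matching simultaneous intervals. If the sponsor wants such intervals, keeping Bonferroni and stating 98.75% intervals would be a coherent alternative.
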